## 3 Discussion

This study aims to address a critical gap in neuromodulation research by investigating the efficacy of tACS in modulating food cravings and neural oscillations. While prior studies have demonstrated that non-invasive brain stimulation techniques such as tDCS and rTMS can influence craving-related behaviors, their effects on oscillatory coherence and large-scale network dynamics remain less explored (Parvaz et al., 2011; Koob and Volkow, 2016; Schwab et al., 2019). tACS, in contrast, offers the unique advantage of directly entraining neural oscillations at behaviorally relevant frequencies, potentially leading to more robust and sustained changes in food cravings.

Craving-related behaviors are increasingly understood as arising from dysregulated interactions between cortical control regions and subcortical rewards circuits. Disrupted connectivity between the prefrontal cortex and structures such as the striatum and amygdala has been implicated in impulsivity and the inability to exert inhibitory control over salient food cues (Chen et al., 2017; Burnette et al., 2019; Liu et al., 2023). By applying tACS over key cortical hubs, including the DLPFC, ACC, and insula at behaviorally relevant frequencies (alpha and theta), this study targets three components of the triadic model of craving: the reflective, impulsive, and interoceptive systems. This frequency-region pairing allows for a hypothesis-driven investigation of how specific oscillatory regimes influence discrete components of craving regulation.

Previous work has linked elevated theta and beta oscillatory activity in fronto-striatal and amygdala networks with increased craving and diminished inhibitory control (Cavanagh and Frank, 2014; Koob and Volkow, 2016; Zavala et al., 2017). tACS has already demonstrated efficacy in modulating such rhythms in cognitive domains such as attention and working memory (Herrmann et al., 2013; Wischnewski and Schutter, 2015) and may exert similar benefits in the context of food addiction. If successful, this study will provide empirical evidence that modulating the frequency-specific dynamics of craving-related networks can lead to measurable behavioral and neural changes in food-related impulse regulation.

By combining high-resolution EEG and fMRI, this study is positioned to provide a multimodal characterization of how tACS influences both oscillatory activity and large-scale network interactions. EEG will allow for the assessment of immediate entrainment and aftereffects, including changes in spectral power, PLV, and ERPs. fMRI, in turn, will assess the spatial and functional reconfiguration of networks via seed-based connectivity and independent component analysis. Particular attention will be paid to connectivity within and between the DLPFC, ACC, insula, amygdala, and striatum. It is expected that alpha-band tACS applied to the DLPFC will enhance top-down control and strengthen connectivity with subcortical structures involved in rewards regulation, while theta-band stimulation of the ACC and insula may normalize aberrant activity in the impulsive and interoceptive systems. This convergence of oscillatory and connectivity-based evidence may validate tACS as a network-level intervention for food craving regulation.

Moreover, the integration of behavioral data, including validated craving questionnaires and Go/No-Go task performance, will allow for a direct correlation between neurophysiological changes and observable cognitive and affective outcomes. The inclusion of both trait- and state-level craving assessments (T-FCQ, S-FCQ, FCI) strengthens the design by capturing both enduring tendencies and momentary fluctuations in craving behavior. When combined with EEG and fMRI findings, these behavioral metrics will provide a comprehensive, multidimensional index of tACS efficacy.

Despite these strengths, several limitations warrant consideration. The relatively brief intervention duration of seven sessions may not fully capture the long-term potential of tACS to modify eating behaviors. Longitudinal studies with extended intervention periods are needed to examine the durability of neural and behavioral changes. Furthermore, individual variability in tACS responsiveness remains a challenge. Factors such as baseline oscillatory state, cortical anatomy, and skull conductivity can influence current distribution and entrainment efficacy (Saturnino et al., 2017). Although individualized modeling using structural MRI and the ROAST pipeline will optimize electrode placement and predict electric field strength, future research should explore real-time, closed-loop tACS protocols tailored to ongoing neural dynamics.

Another limitation relates to the inherent temporal and spatial trade-offs of EEG and fMRI. While EEG provides high temporal resolution, it cannot localize activity with the precision of fMRI. Conversely, fMRI offers excellent spatial resolution but limited insight into fast oscillatory dynamics. Simultaneous EEG-fMRI recordings could enhance future studies by capturing both the timing and spatial footprint of tACS-induced network changes. Moreover, functional connectivity measures are inherently correlational and cannot establish causality. Incorporating task-based fMRI with causal modeling approaches may provide a more mechanistic understanding of network reorganization.

A limitation of the within-subject design for the FA^–^ group is the absence of a washout period between active and sham sessions, which is also acknowledged. Although the sessions are counterbalanced and scheduled 24 h apart, previous research suggests that tACS aftereffects, especially at theta frequencies, may persist for several hours and potentially influence subsequent neural activity or behavioral responses (Herrmann et al., 2013; Wischnewski and Schutter, 2015). This temporal proximity may introduce residual effects, which will be accounted for in statistical analyses and acknowledged in interpretation.

It is also important to acknowledge that the study targets cortical regions involved in craving regulation. However, the broader aim is to engage large-scale neural networks that underlie self-control, salience detection, and interoceptive awareness. Although tACS cannot directly stimulate deep structures like the striatum or amygdala, frequency-specific entrainment of cortical hubs, such as the DLPFC, ACC, and insula, may drive network-level reorganization through their anatomical and functional connectivity. These regions are key nodes in the Salience Network, which governs the detection and prioritization of internal and external stimuli, and dynamically interacts with both the Default Mode Network and Executive Control Network (Parvaz et al., 2011; Volkow and Morales, 2015; Koob and Volkow, 2016).

The integration of EEG, fMRI, and behavioral data is expected to yield converging evidence on the neural mechanisms of tACS-induced craving modulation. We anticipate that frequency-specific changes in EEG spectral power and phase-locking will correlate with enhanced connectivity in prefrontal-subcortical networks observed via fMRI, and with improvements in behavioral indices of craving control, such as reduced subjective craving and improved inhibitory task performance. These multimodal relationships will help to validate neural markers that predict treatment responsiveness. Importantly, by using established craving scales and ecologically valid tasks, this protocol enhances the translational potential of tACS interventions in real-world settings, such as clinical programs targeting obesity or compulsive eating.

Finally, while this study focuses on food cravings, the theoretical framework and methodological approach have potential relevance to a broader range of compulsive and addictive behaviors. Given the shared neurocognitive mechanisms underlying substance use disorders, binge eating disorder, and impulse control deficits (Volkow and Morales, 2015; Volkow et al., 2019), findings from this protocol may support future clinical applications of tACS across multiple domains of addiction medicine.

In conclusion, this study protocol outlines a novel, multimodal investigation of the efficacy of tACS in modulating craving-related network activity, cognitive control, and subjective experience. By combining EEG, fMRI, and behavioral data within a rigorously controlled experimental design, it seeks to elucidate the neurophysiological mechanisms underlying craving regulation and the potential of oscillation-based neuromodulation for clinical intervention. If the anticipated effects are confirmed, this study will lay the groundwork for more personalized, frequency-targeted treatments for FA and related disorders, advancing both the theoretical understanding and therapeutic potential of non-invasive brain stimulation.

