## 2 Methods

### 2.1 Study design

This randomized, double-blind, sham-controlled, parallel-group trial is designed to investigate the effects of fixed-frequency transcranial alternating current stimulation (tACS) on food cravings, inhibitory control, and associated neural oscillations. The study includes participants with and without food addiction, classified according to the Yale Food Addiction Scale 2.0 (YFAS 2.0).

Participants classified as food-addicted (FA+) will be randomly assigned to one of four intervention arms: (1) active tACS targeting the anterior cingulate cortex (ACC) at a theta frequency of 6 Hz, (2) active tACS targeting the dorsolateral prefrontal cortex (DLPFC) at an alpha frequency of 10 Hz, (3) active tACS targeting the insula at a theta frequency of 6 Hz, or (4) sham tACS serving as a placebo control.

Participants classified as non-addicted (FA-) will be assigned to a separate fifth group. This group will follow a within-subject, counterbalanced crossover design in which each participant receives both active and sham stimulation across two sessions. Sessions will be scheduled on consecutive days, with a 24-h interval, and the stimulation order randomized to mitigate order effects. This approach enables within-subject comparison of stimulation effects in individuals without food addiction and allows for additional between-group analyses contrasting FA+ and FA- responses. Furthermore, the crossover approach in the FA- group is selected to reduce unnecessary stimulation exposure and focus statistical power on the primary FA+ comparisons, while still enabling exploratory within-subject analyses in non-addicted participants.

This design allows for direct comparisons between active and sham conditions and across cortical targets while also enabling exploration of craving-related network dynamics in the presence and absence of FA.

Randomization will be conducted using a computerized block randomization algorithm, stratified by food addiction status (FA+ vs. FA-). To ensure allocation concealment, the randomization sequence will be generated by a researcher not involved in data collection or analysis. All participants, tACS administrators, and outcome assessors will remain blind to group allocation throughout the study.

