Data management will be conducted in accordance with ethical data protection standards. All data will be stored on a secure, encrypted server with access limited to authorized personnel. Personal identifiers will be removed and replaced with anonymized participant codes. Missing data will be handled using multiple imputations via chained equations (MICE), assuming data are missing at random. Sensitivity analyses will be conducted to test the robustness of findings under different imputation models.

All statistical analyses will follow an intention-to-treat approach. The primary outcome–change in S-FCQ and FCI scores–will be analyzed using repeated measures ANOVA, with time (pre/post) and group (stimulation target and sham) as factors. *Post hoc* comparisons will be corrected using the Bonferroni method. Changes in Go/No-Go performance will be analyzed using ANCOVA, adjusting baseline reaction times and error rates. EEG parameters will be analyzed using linear mixed-effects models to account for within-subject correlations across sessions. Functional connectivity changes in fMRI will be assessed using seed-based and ICA models, with between-group comparisons conducted using *t*-tests or mixed models where appropriate. Longitudinal changes in YFAS and T-FCQ scores will be modeled using hierarchical linear regression.

Exploratory analyses will examine whether individual differences in sex, BMI, and baseline craving severity moderate the effects of tACS. Clustering methods will also be used to identify subgroups based on EEG and fMRI response profiles.

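### Correlations among post-stimulation changes, and clusters built on them, cannot by themselves show who responds to tACS; the marker claim needs a baseline-marker-by-arm test against sham or should be limited to candidate markers

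*Protocol article*

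**What the plan says.** The marker claim is in the protocol article, section 3 (Discussion). The authors anticipate that "frequency-specific changes in EEG spectral power and phase-locking will correlate with enhanced connectivity in prefrontal-subcortical networks observed via fMRI", and that these changes will also go with less craving and better inhibitory performance. They conclude: "These multimodal relationships will help to validate neural markers that predict treatment responsiveness". Earlier in the same section, the combination of craving questionnaires and Go/No-Go data "will allow for a direct correlation between neurophysiological changes and observable cognitive and affective outcomes". None of these sentences names an arm or a comparison with sham.

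Section 2.5 (Data collection and analysis) adds, in its exploratory paragraph: "Clustering methods will also be used to identify subgroups based on EEG and fMRI response profiles". The moderation analysis in that paragraph covers three characteristics, none of them neural: "Exploratory analyses will examine whether individual differences in sex, BMI, and baseline craving severity moderate the effects of tACS".

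The trial has the comparator it would need. Section 2.1 lists, among four randomised arms for food-addicted (FA+) participants, "4) sham tACS serving as a placebo control", and says: "This design allows for direct comparisons between active and sham conditions". Section 2.5 also plans to analyse connectivity change "with between-group comparisons conducted using" t-tests or mixed models. That compares connectivity change between arms. It does not ask whether the relation between a neural measure and the outcome differs between arms.

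**The concern.** A marker that predicts response to tACS has to separate participants who gain from stimulation from those whose craving would have changed anyway. That takes a measure not itself altered by treatment, and evidence that its relation to outcome differs between active and sham.

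The relations in the Discussion are of another kind. They link one pre-to-post change with another in the same person. Arousal, hunger and habituation to food images could plausibly shift EEG, connectivity, craving scores and task performance together, and would do so under sham as well. A correlation between such changes is then expected even if tACS does nothing. Subgroups formed from response profiles share the weakness, because membership is defined by what happened after randomisation.

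At stake is the use made of the result. The Discussion goes on to mention clinical programmes and more personalised, frequency-targeted treatment. A marker of whose craving happened to change would be a poor basis for choosing whom to stimulate.

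**Working it through.** The plan gives no figure for the marker or cluster analysis, so there is none to reproduce. The check asks how often a change-change correlation would be significant with no tACS effect, and what a contrast with sham does to that.

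**Inputs**
- 140 FA+ participants in four parallel arms (section 2.2.5). Equal allocation is assumed: 35 per arm, so 105 active and 35 sham.
- With 20% lost, the dropout rate named in section 2.2.5: 84 active and 28 sham.
- Two-sided test at 0.05.
- The correlation r between neural change and craving change is not in the article. It is assumed equal in every arm, sham included, and varied from 0.1 to 0.4.

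**Step 1: correlation without a sham contrast.** On the Fisher scale the test statistic is centred at atanh(r) × √(n − 3), and the chance of significance is Φ(that value − 1.96) plus a negligible opposite tail. For r = 0.3 and n = 105: 0.3095 × √102 = 3.126, and Φ(3.126 − 1.96) = Φ(1.166) = 0.88.

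**Step 2: active versus sham.** The statistic is [atanh(r_active) − atanh(r_sham)] / √(1/(n_active − 3) + 1/(n_sham − 3)). With equal r in both groups it is centred at zero, so it should reject in about 5% of trials.

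Simulation of 20,000 trials per setting, with bivariate normal changes and no tACS effect, gave these rates of significance:

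| Assumed r in every arm | 105 active alone | 84 active alone | One arm of 35 alone | Active-versus-sham contrast |
|---|---|---|---|---|
| 0.1 | 17% | 15% | 9% | about 5% |
| 0.2 | 54% | 45% | 21% | about 5% |
| 0.3 | 88% | 79% | 43% | about 5% |
| 0.4 | 99% | 97% | 69% | about 5% |

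**Step 3: pooling sham without an arm term.** This does not help. With all 140 participants the step 1 formula uses √137 = 11.70. For r = 0.1: 0.1003 × 11.70 = 1.174, giving 22%. For r = 0.3: 0.3095 × 11.70 = 3.62, giving Φ(1.66) = 95%. The rate rises because the sample is larger. What protects the inference is the contrast between arms, not the presence of sham data.

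**Step 4: price of the contrast.** With a standardised marker and unit residual variance, the standard error of an arm's slope is about 1/√n. The slope difference detectable with 80% power is about 2.8 × √(1/105 + 1/35) = 0.55 for all active versus sham, and 2.8 × √(2/35) = 0.67 for one active arm versus sham. The Fisher formula, with no correlation under sham, gives a similar detectable active correlation for 105 versus 35: tanh(2.80 × √(1/102 + 1/32)) = tanh(0.568) = 0.51.

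**The case against.** The strongest reply is that the Discussion describes hopes rather than a planned analysis. Section 2.5 lists no correlation of neural with behavioural change, and a condensed article may leave such detail to a full protocol or analysis plan. That is right about missing detail, and its absence is not the point here. The Discussion does state an inference, from correlated changes to predictive markers, and that inference fails however the correlations are computed.

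Four stronger readings are tempting, and the article does not support them:

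- **That sham will be left out.** No sentence restricts the correlations or clusters to active arms, and active-versus-sham comparison is a stated feature of the design.
- **That a validated marker will be reported.** The wording is that the relations will help to validate markers. The Discussion also concedes that connectivity measures are correlational and cannot establish causality. That caveat is not carried over to the marker sentence.
- **That clusters will be called responders and compared on craving.** The clustering is exploratory, and no such label or test is named, so no error rate is attached to it here.
- **That fMRI change cannot precede the outcome.** Section 2.4 names imaging on Days 0 and 8 only, but section 2.5 and the Figure 1 caption add a scan on Day 2. That scan precedes the Day 5 and Day 8 craving and Go/No-Go assessments.

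It is also fair to say that the percentages above are power to detect a correlation assumed to be real. The correlation would exist; the error would lie in reading it as a response to tACS. At r = 0.1 in a single arm the rate is only 9%.

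**Conclusion.** The point holds as a minor one. Correlations among post-stimulation changes, and clusters of response profiles, cannot by themselves show who responds to tACS. The only moderators stated are sex, BMI and baseline craving severity, so the article names no neural-marker analysis that would support the conclusion in the Discussion.

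The risk is that ordinary co-variation could be presented as a predictive marker. Its size is illustrative: 17% to 99% of trials for r = 0.1 to 0.4 with 105 active participants, against about 5% for a contrast with sham. These figures assume equal allocation, bivariate normal changes, no tACS effect and the same correlation in every arm. The article gives no value for that correlation, and a value of zero would bring the rate back to 5%. Primary and secondary efficacy analyses are unaffected.

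**What to change.** 1. In section 2.5, define the test of predictive markers as an exploratory marker-by-arm (active versus sham) interaction. Use ANCOVA of Day 8 craving and Go/No-Go, adjusted for the Day 1 pre-stimulation score. Take the markers from pre-treatment data: Day 0 fMRI and Day 1 pre-stimulation EEG. Call a marker predictive only if its slope differs from the sham slope.
2. Form the clusters from the same pre-treatment data and test cluster-by-arm. If response-profile clusters are kept, make them descriptive, include sham participants and report the sham share of each cluster.
3. Treat early on-treatment changes (Day 1 post-minus-pre EEG, Day 2 fMRI) as descriptive only. They come before the later outcomes but after randomisation.
4. In the Discussion, replace *validate* with *nominate candidate*.

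The cost is text and analysis time; every measure is already scheduled. The downside is lower sensitivity. With 35 per arm and 80% power, the interaction detects a standardised slope difference of about 0.55 (all active versus sham) or 0.67 (one arm versus sham), and dropout would raise both. The realistic yield is therefore candidate markers for a later study.

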## 4 Ethics and dissemination

This study will be conducted in accordance with the ethical principles outlined in the Declaration of Helsinki and complies with international guidelines for human subject research. Ethical approval has been sought from both the Abu Dhabi Health Research and Technology Committee (ADHRTC) and the Human Research Ethics Committee of the United Arab Emirates University (UAEU-HREC). Final approval will be obtained prior to initiating participant enrollment.

All participants will provide written informed consent prior to participation. During the consent process, participants will be informed of the study’s objectives, procedures, potential risks and benefits, confidentiality safeguards, and their right to withdraw at any time without penalty or loss of entitlements. Consent will be obtained in a private setting and documented electronically and in writing.

To ensure participant safety, rigorous exclusion criteria have been implemented to minimize risks associated with tACS and MRI procedures. Adverse events will be closely monitored throughout the study, and any serious or unexpected effects will be reported to the ethics committees in accordance with regulatory standards. Participants experiencing adverse effects will be offered appropriate support and may be withdrawn from the study if necessary.

Confidentiality will be maintained by assigning a unique study ID to each participant. All identifiable data will be securely stored and accessible only to authorized members of the research team. De-identified data will be used for analysis, publication, and data sharing. Data handling and storage procedures will comply with institutional and national data protection regulations.

Any protocol amendments, including changes to eligibility, intervention procedures, or outcome assessments, will be submitted for ethics committee approval and documented in trial records. The study will be registered in a publicly accessible clinical trial registry before participant enrollment, and findings will be disseminated through peer-reviewed publications and conference presentations in accordance with open science principles.
